# Patients and Methods

## Study Design

### General Design

This study is a case-control study utilizing a repeated measure design. Each participant will undergo a series of bronchial challenges trials, including

- Mannitol challenge
- Methacholine challenge
- Placebo (control) challenge.

Vascular parameters such as flow mediated dilation (FMD; endothelial function) and pulse wave velocity (PWV; arterial stiffness) will be evaluated before, immediately after, 1 hour after, and 24 hours after each challenge. Blood samples will be obtained for analysis of systemic inflammatory response and exhaled breath condensate will be collected for analysis of pulmonary inflammation and oxidative stress at each time-point.

For the secondary objective, the subjects will in a random order either exercise for 30 minutes or rest for 30 minutes before being subjected to either a placebo challenge or a mannitol challenge, in a cross-over design. The same parameters as for the primary objective will be evaluated before, immediately after, 1 hour after, and 24 hours after each challenge.

1. ***Case-control studies***

*Definition of study groups:*

Asthmatics, defined according to CTS criteria[^22^](#_ENREF_22), will be recruited for the study. This repeated measure design will minimize the risk of between-groups variability and match the case and the control group on all variables except the experimental parameters within the different trails.

*Blinding and avoiding bias:*

All subjects will be blinded to what bronchial challenge is administered. The challenges will be administered in random order and the research staff performing the vascular function analysis will be blinded to what challenge the participant has undergone within each trail.

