*Arterial stiffness* - Arterial stiffness will be evaluated using pulse wave velocity (PWV) between the carotid and femoral arteries. After 10 minutes of supine rest, the time of the up-stroke of 30 pulse waves will be collected simultaneously using applanation tonometry (Mikro-tip Catheter Transducers model SPT-301, MillarInstruments, Inc., Houston, TX, USA) over the femoral and the carotid arteries. The sites of measurement will be temporarily marked, whereby the distances between the markings and the sternal notch will be measured. The tonometry signal will be recorded using the Powerlab acquisition system (Powerlab, 16/30, ADInstruments, New South Wales, Australia). A total of 10 consecutive beats will be selected for analysis (LabChart version 7.3.5 ADInstruments, New South Wales, Australia) and the timing of each upstroke will be manually adjusted to minimize potential errors throughout the steps of analysis. After receiving a time-stamp for each beat, delta-time (Δt) will be calculated as the difference between the time of the up-stroke of the waveform at the femoral artery and the carotid artery (Δt = femoral waveform – carotid waveform). The distance (d) will be calculated as the difference between the distance from the sternal notch to the femoral artery and the sternal notch to the carotid artery. PWV was then calculated as d/Δt and expressed in meters per second (m/s)[^31^](#_ENREF_31). Beat-to-beat blood pressure will be measured throughout the test (Finapres Medical Systems, Amsterdam, The Netherlands) and the signal will be calibrated offline to brachial blood pressure also recorded at the time of testing. The heart rate will be monitored using 1-lead echocardiography (Dual Bio Amp, ADInstruments, New South Wales, Australia).

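### Pulse wave velocity depends on the reader's choice of beats and manual upstroke adjustment, but the stated blinding covers only the challenge, not exercise versus rest or time point

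*Protocol*

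**What the plan says.** Protocol section 3.3, Study Procedures (Arterial stiffness), describes the PWV reading in three steps.

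- Recording: "the time of the up-stroke of 30 pulse waves will be collected simultaneously using applanation tonometry".
- Selection: "A total of 10 consecutive beats will be selected for analysis".
- Adjustment: "the timing of each upstroke will be manually adjusted to minimize potential errors throughout the steps of analysis".

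Δt is the femoral upstroke time minus the carotid upstroke time, and PWV is distance divided by Δt. The section gives no rule for which run of ten is kept and no criterion for moving an upstroke.

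Section 3.1.1, General Design, states the blinding of analysts: "the research staff performing the vascular function analysis will be blinded to what challenge the participant has undergone within each trail". For the secondary objective the same section adds another randomised factor: "the subjects will in a random order either exercise for 30 minutes or rest for 30 minutes before being subjected to either a placebo challenge". The alternative to placebo there is mannitol. Section 3.1.3 makes PWV a secondary outcome. Section 3.4.2 analyses Aim 1 with a two-way ANOVA (trial and time) and Aim 2 with a three-way ANOVA (exercise or rest, challenge or placebo, and time).

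**The concern.** The reader has two points of discretion: where the run of ten starts, and where each upstroke is placed. Both feed Δt, so both feed PWV. The protocol recognises the risk of reader bias and blinds analysts to the challenge, the factor tested in Aim 1. It does not state that this extends to exercise versus rest, the factor added for Aim 2, or to time point.

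A reader who knew that a file came from an exercise day, or from after a challenge, could read it in line with expectation without intending to. Randomising the order of conditions does not guard against this, because the error enters at reading. At stake are the exercise main effect and the exercise-by-time effect on PWV.

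**Working it through.** **1. Which contrasts are exposed.** Write the reader's average shift in a PWV reading as β, which may depend on what the reader knows. With the stated blinding, β cannot depend on the challenge. At worst it depends on exercise or rest (E, R) and on time (t, with 0 for baseline): β(E,t) and β(R,t). The bias in each contrast is then:

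| Contrast | Bias | Result |
|---|---|---|
| Aim 1 trial-by-time | [β(t) − β(0)] − [β(t) − β(0)] | cancels |
| Aim 2 exercise-by-challenge | [β(E) − β(R)] − [β(E) − β(R)] | cancels |
| Aim 2 exercise main effect | average over t of β(E,t) − β(R,t) | remains |
| Aim 2 exercise-by-time | [β(E,t) − β(E,0)] − [β(R,t) − β(R,0)] | remains |

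The time main effect, β(t) − β(0), is exposed by the same algebra, but Aim 1's stated test is the interaction. The cancellation is approximate. A shift δ in Δt changes PWV by about −(PWV²/d) × δ, so the same δ has a somewhat different effect where PWV itself differs.

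**2. How sensitive a reading is.** The documents give no path length, PWV level or reader error. Assume a path of 0.45–0.55 m and PWV of 6–8 m/s.

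- Δt = d/PWV runs from 0.45/8 = 56 ms to 0.55/6 = 92 ms.
- At 0.50 m and 7.0 m/s, Δt = 71.4 ms. Shortening it by 2 ms gives 0.50/0.0694 = 7.20 m/s, a change of 0.20 m/s.
- Over the whole assumed range, shortening by 2 ms raises PWV by 0.13–0.30 m/s.

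This shows that placement matters. It does not show that any such shift occurs, still less that it differs between exercise and rest.

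**3. Precision of 10 against 30 beats.** The variance of one reading is sv² + sb²(1 + (m − 1)ρ)/m. Here m is the number of beats, sb the beat-to-beat SD, ρ the correlation between beats and sv the remaining within-subject SD. All values are assumed: sv 0.3–0.8 m/s, sb 0.2–1.0 m/s, ρ 0 or 0.3.

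- Middle case (sv 0.5, sb 0.5, ρ 0): √[(0.25 + 0.025)/(0.25 + 0.0083)] = 1.03.
- Worst case (sv 0.3, sb 1.0, ρ 0): √[(0.09 + 0.10)/(0.09 + 0.0333)] = 1.24.
- With sb at most 0.5 m/s, the SD with 10 beats is 1.00–1.08 times that with 30.

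The √3 = 1.73 factor applies only to the beat-to-beat part of the error, and only if beats are independent.

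**4. The plan's own figure.** Section 3.4.1 states 20 subjects per group for FMD, with no difference or SD, so it cannot be reproduced. It does not concern PWV and is not affected by this point.

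**The case against.** The strongest reply is that the protocol is silent and does not say that readers are unblinded. A reader might infer that analysts know the exercise condition and time point. The documents do not support that; they support only that such blinding is not stated.

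Other stronger readings also go too far.

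- **Free choice of beats.** The text requires a consecutive run, so single beats cannot be picked. If the 30 waves form one continuous recording, the choice is among 30 − 10 + 1 = 21 starting positions.
- **Material loss of precision.** The losses under step 3 are mostly small and rest on assumed values. Choosing a clean run and correcting misplaced upstrokes may reduce error, which is the protocol's stated purpose.
- **Automatic placement is needed.** Manual or automatic placement is a matter of preference, and nothing in the protocol makes manual placement wrong.
- **A known bias of a few milliseconds.** Because Δt is a difference, a habit applied equally to both waveforms cancels within each beat. A shift common to all conditions largely cancels within the subject. Only a shift that differs between sites and also between conditions matters, and no figure in the documents gives its size. If a 0.2 m/s shift did follow exercise, with a paired-difference SD of 0.5–1.0 m/s, a nominal 5% two-sided test would err about 15–43% of the time at 20 subjects. That figure is conditional on a supposed bias and applies to a simple exercise-versus-rest comparison, not to the interaction with challenge.

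It can also be said that reading rules belong in a laboratory procedure or an analysis plan not shown here. That is fair for the detail of upstroke placement. It is weaker for blinding, because the protocol itself states the rule and names only the challenge.

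**Conclusion.** The point holds in a limited form and is minor. PWV is operator-dependent as described, and the stated blinding does not extend to exercise versus rest or to time point. This leaves the exercise main effect and the exercise-by-time effect on a secondary outcome open to reader bias. Aim 1's trial-by-time test and the exercise-by-challenge interaction are largely protected, provided the challenge blinding works and a reader's shift is similar across challenges. The size of any bias cannot be derived from the documents, and the millisecond calculations show sensitivity only.

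**What to change.** In section 3.1.1, state that recorded vascular files are given random codes and read offline in random order, by analysts blind to challenge, exercise or rest, and time point. The existing sentence covers vascular analysis as a whole, so one wording would serve PWV and FMD, although no FMD reading problem is shown here.

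In section 3.3 (Arterial stiffness), fix before any file is read which beats are used: for example, all beats that meet a set quality criterion, or the first acceptable run of ten. Manual adjustment can stay.

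The cost is a change of wording and a little file-coding and reading time. Blinding will not be perfect, because heart rate in the trace may partly reveal recent exercise; a fixed beat rule gives some protection where that happens.

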## Statistical Plan

### Sample Size Determination

We do not know the anticipated effect of our interventions on FMD; however, based on previous studies[^8^](#_ENREF_8), a total of 20 subjects per group will be sufficient to detect a difference in FMD between trials (α=0.05, power=0.8). An additional 10 subjects per group will be recruited to account for dropouts. Thus, 60 subjects will be recruited for aim 1 and 60 subjects will be recruited for aim 2.

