# Introduction/Significance

This document is a clinical research protocol and the described study will be conducted in compliance with the protocol, Good Clinical Practices standards and associated Federal regulations (i.e Health Canada), and all applicable institutional research requirements.

Asthma is a chronic inflammatory disease characterized by pulmonary inflammation and bronchoconstriction, and the prevalence of asthma is steadily rising worldwide[^1^](#_ENREF_1). **Asthma and Cardiovascular Disease:**  While asthma is generally considered to be a disease of the airways, there are important systemic consequences which have predisposed people with asthma to become more likely to die from cardiovascular (CV) disease compared to non-asthmatics[^2^](#_ENREF_2). Additional CV risks have been reported in people with severe asthma[^3^](#_ENREF_3), and there is a relationship between reductions in lung function and cardiac death[^4^](#_ENREF_4). To date, little is known in regards to the interaction between asthma exacerbations and CV risk. **Asthma and vascular dysfunction:** Brachial flow-mediated dilation (FMD) is used as a non-invasive tool to evaluate endothelial function[^5^](#_ENREF_5). Brachial FMD is impaired in people with coronary dysfunction[^6^](#_ENREF_6), and can predict future CV events better than traditional CV risk factors[^7^](#_ENREF_7). People with asthma have previously been shown to have impaired endothelial function compared to non-asthmatics[^8^](#_ENREF_8), but the underlying mechanism(s) are unclear. **Asthma, Systemic Inflammation, and CV risk:** Chronic systemic inflammation is an established risk factor and predictor of future CV events[^9^](#_ENREF_9), and levels of systemic inflammation are increased in asthma[^10^](#_ENREF_10)^,^[^11^](#_ENREF_11). Furthermore, while people with high levels of inflammation are more likely to suffer both first time and recurrent cardiac events[^12^](#_ENREF_12)^,^[^13^](#_ENREF_13), levels of systemic inflammation in asthma are related to disease severity and are the highest during asthma exacerbations[^10^](#_ENREF_10)^,^[^11^](#_ENREF_11). Previous studies have shown that systemic inflammation directly impairs vascular function[^14^](#_ENREF_14), and rodent work has shown that pulmonary inflammation can impair vascular function[^15^](#_ENREF_15). To-date no study has examined how an asthma attack may affect vascular function and CV risk. Thus, to gain better understanding of the increased CV risks associated with asthma exacerbations, *the first aim of this study is to evaluate how acutely increasing pulmonary inflammation affects vascular function* in people with asthma. **Physical activity and the immune system:** Physical inactivity has previously been associated with increased systemic inflammation[^16^](#_ENREF_16), while higher levels of physical activity can reduce inflammation[^17^](#_ENREF_17) and vascular dysfunction[^18^](#_ENREF_18)^,^[^19^](#_ENREF_19). Acute exercise has been shown to modulate the systemic responses to inflammatory insults[^20^](#_ENREF_20), and being more physically active is associated with better asthma symptoms[^21^](#_ENREF_21) but whether acute exercise influences the systemic responses to asthma exacerbations is unknown. The second aim of this study is to *assess the influence of acute exercise on the systemic and vascular responses to acute pulmonary inflammation* in asthma.

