**2. Material and Supply**

**Asthma Challenges Kits**: Methacholine challenges will be performed on 16 subjects to evaluate the inflammatory and vascular responses to bronchoconstriction. Mannitol challenges will be evaluated on the same 16 subjects during rests and following acute exercise, i.e. a total of 32 mannitol challenges will be conducted.

| Aridol (Mannitol) 32 X $80.14 | $2,564 |
| --- | --- |
| Methacholine 16 X $50.00 | $800 |
| **Total Asthma Challenges Kits** | **$3,364** |

**Exhaled Breath Condensate (EBC)**: EBC will be collected using the RTube™ EBC collector before and 1 and 24 hour following each asthma challenge (4 challenges X 16 subjects X 3 time-points = 192 samples) for analysis of CRP (see attached quote from Eve technologies).

| RTube™ EBC 100 kit (2x) | $6,060 |
| --- | --- |
| EBC analysis (attached quote) CRP (n=192) | $3,720 |
| **Total EBC** | **$9,780** |

**Systemic Inflammatory Markers**: Venous blood will be collected and processed for serum analysis before and 1 and 24 hour following each asthma challenge (4 challenges X 16 subjects X 3 time-points = 192 samples) for analysis of IL-6, TNFα, CRP (see attached quote from Eve technologies). The anti-inflammatory cytokine IL-10 will be analyzed serum before and 1 and 24 hour following the exercise/mannitol challenge (1 challenge X 16 subjects X 3 time-points = 48 samples).

| Blood collection supplies (vacutainers, alcohol wipes, needles) | $500 |
| --- | --- |
| Blood analysis (see attached quote) |  |
| IL-6, TNFα, CRP (n=192 in duplicates (384)) and IL-10 (n=48 in duplicates (96)) | $9,698 |
| **Total Systemic Inflammatory Markers** | **$10,198** |
|  |  |

**Other Supplies**: A CPET will be performed on all participants to determine peak oxygen consumption. Respiratory gas exchange data will be obtained, with oxygen consumption, ventilation, heart rate, rating of perceived exertion and dyspnea recorded. All will perform the test with a 12-lead ECG. These funds are required as all these expendables are needed to do our basic experiments.

| Metabolic Measurement: mouthpieces, mouth filters, ECG electrodes, pulse oximetry electrodes, ultrasound jelly. | $500 |
| --- | --- |
| **Total Other Supplies** | **$500** |

| **Total Material and Supplies** | **$23,842** |
| --- | --- |

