**3. Payment to Study Subjects**

**Parking and Honoraria**: All research participants will be reimbursed for parking at the University of Alberta East Parkade (4 challenges X 2 days X 16 participants = 128 visits). Participants who complete all parts of the study will receive a $200 gift card (on average - $25/visit) at their choice.

| Parking ($7/day) | $896 | |
| --- | --- | --- |
| Honoraria ($200/subject) | $3,200 | |
| **Total Payment to Subjects** | | **$4,096** |

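### The sample size is counted per parallel group in a single-cohort repeated-measures study, conflicts with the 16 people planned in the budget appendix, and carries an 80% power claim that cannot be checked

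*Protocol*

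**What the plan says.** Section 3.4.1 (Sample Size Determination) begins with an admission: "We do not know the anticipated effect of our interventions on FMD". It then relies on an earlier study (reference 8) to state that "a total of 20 subjects per group will be sufficient to detect a difference in FMD between trials" ("α=0.05, power=0.8"). Ten more per group are added for dropout, and the paragraph ends: "Thus, 60 subjects will be recruited for aim 1 and 60 subjects will be recruited for aim 2".

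Section 3.1.1 (General Design) describes a different structure. "Each participant will undergo a series of bronchial challenges trials", namely mannitol, methacholine and placebo. Aim 2 is a cross-over of exercise or rest before a mannitol or placebo challenge. Only people with asthma are recruited. The section uses the words case and control group, but explains that these are matched because the same people appear under different trials.

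Appendix 1 (Budget) gives a third picture. Under Material and Supply, methacholine is planned for 16 people, and "Mannitol challenges will be evaluated on the same 16 subjects during rests and following acute exercise". Under Payment to Study Subjects the visit count is "4 challenges X 2 days X 16 participants = 128 visits".

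The Introduction cites reference 8 for one statement: "People with asthma have previously been shown to have impaired endothelial function compared to non-asthmatics".

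**The concern.** The number of people enrolled belongs in the protocol, and here it is given in two ways that cannot both be true: 60 plus 60 in section 3.4.1, and 16 for everything in Appendix 1. The unit of counting in section 3.4.1 (the group) does not exist as a parallel arm in the design. The power statement has no effect size behind it, and the protocol cites its only source for a comparison between different people, whereas the trial measures an acute change within the same people.

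At stake is whether an ethics board, a funder or a reader of the results can tell how many people will undergo bronchial provocation, and what size of change in FMD the study could detect.

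**Working it through.** **Inputs.** From section 3.4.1: alpha 0.05 (sidedness not stated; two-sided assumed), power 0.80, 20 per group, plus 10 for dropout, 60 per aim. Not given anywhere: the difference in FMD, its SD, the within-person correlation. From Appendix 1: 16 people, four challenges each.

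**1. The stated total.** 20 + 10 = 30 per group, which is 20 / (1 − 1/3), a one-third dropout allowance. 60 / 30 = 2, so each aim's total requires exactly two groups. Against the design:

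| Reading | Total |
|---|---|
| One within-person cohort | 30 |
| Aim 1, three trials counted as groups | 30 × 3 = 90 |
| Aim 2, four conditions counted as groups (exercise/rest × mannitol/placebo, as the three-way ANOVA in section 3.4.2 implies) | 30 × 4 = 120 |
| Stated for each aim | 60 |

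Neither aim, as designed, has two parallel groups.

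**2. Is 16 a slip?** Mannitol challenges: 2 × 16 = 32. Samples: 4 × 16 × 3 = 192. Visits: 4 × 2 × 16 = 128. Parking: 128 × $7 = $896. Honoraria: 16 × $200 = $3,200. Every line agrees, so 16 is a consistent plan covering both aims.

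**3. Can the 80% be reproduced?** No, because no effect, SD or correlation is stated. One can only solve backwards for the effect that each number would detect (t-test, two-sided 0.05, 80% power).

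- Two independent groups of 20: a difference of 0.91 SD.
- Paired comparison: find dz = (mean within-person difference) / (SD of that difference) such that a noncentral t with n − 1 degrees of freedom and noncentrality dz × √n gives power 0.80.

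| Completers | Where the number comes from | Detectable dz |
|---|---|---|
| 16 | Appendix 1 | 0.75 |
| 20 | Section 3.4.1, read as completers in one cohort | 0.66 |
| 40 | 60 recruited less one third | 0.45 |

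**4. How far power depends on the missing effect.** The dz values below are assumptions, chosen only to show the range.

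| Assumed dz | n = 16 | n = 20 | n = 40 |
|---|---|---|---|
| 0.3 | 20% | 25% | 46% |
| 0.5 | 46% | 56% | 87% |
| 0.8 | 85% | 92% | >99% |

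Any of these could apply. The document gives no means of choosing among them.

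**The case against.** Four points can be made for the plan.

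*The figures 20, 30 and 60 are steps in one calculation.* True: evaluable per group, recruited per group, total per aim. The real conflict is 60 plus 60 against 16, together with the silence in section 3.4.1 on whether the two aims share participants.

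*The design section does name a case and a control group, which may be where the factor of two comes from.* Possibly. The same passage shows that they are the same people under different trials, so doubling counts each person twice. Where the 60 came from may be understandable, but it still does not fit the design.

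*Sixteen appears only in a budget.* The appendix is part of the protocol, section 6 repeats its totals, and it fixes how many kits and assays are paid for.

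*Sixteen may be enough.* This stands. A reader might infer that 16 is underpowered because it is below 20, but that depends on what 20 means. If 20 was meant per independent group, it corresponds to 0.91 SD. For 16 paired people, dz = 0.91 / √(2(1 − ρ)), which is 0.77 at an assumed correlation of 0.3 (power 82%) and 0.91 at 0.5 (power 92%). If 20 was meant as completers in one cohort, 16 falls short of it. The protocol does not say which was meant.

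Reference 8 might also supply a usable SD for FMD. The source is not at hand; all that can be said is that the protocol cites it for a contrast between people with and without asthma.

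**Conclusion.** The concern holds as an inconsistency and an unsupported power claim. The counting unit does not fit the design, the total for each aim requires two groups that neither aim has, and the appendix plans fewer people for both aims together than section 3.4.1 calls sufficient for a single group. The 80% power cannot be tied to 16, 20 or 60 people.

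Two stronger conclusions are not supported. A reader might infer that the trial is underpowered. Without an effect, SD or correlation, 80% can be neither confirmed nor refuted. A reader might also infer that 60 plus 60 exposes more people to provocation tests than necessary. With the effect unknown, the number needed is unknown too: 40 completers would be about right for a within-person difference of 0.45 SD.

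The detectable differences of 0.75, 0.66 and 0.45 assume a single paired t-test, two-sided 0.05, with no adjustment for several contrasts or time points. They do not describe the power of the trial-by-time interaction or of the three-way ANOVA in section 3.4.2.

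**What to change.** In section 3.4.1, state one number recruited and one number completing. Say whether aims 1 and 2 share participants and how many sessions each person has. Use the same figures in Appendix 1 under Material and Supply and Payment to Study Subjects. The session count needs stating because the appendix counts four challenges per person, whereas the two aims together imply five distinct conditions if participants are shared and aim 2 has all four combinations.

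Delete the per-group counting from section 3.4.1 and the case-control label from section 3.1.1.

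Replace the 80% claim with the detectable within-person difference for a named contrast and time point in each aim. For aim 1 this could be the change in FMD from baseline, mannitol versus placebo, at a time point the sponsor names; if 16 completers stand, that is 0.75 SD of the paired difference. Aim 2 needs its own statement.

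Cost: rewording one paragraph and aligning the appendix. Restating the figure for the number actually planned adds no patients. If 16 stands, the stated detectable difference is less favourable than with 20 or 40 completers. If the sponsor prefers 20 completers, or 30 recruited, that exceeds what Appendix 1 funds and the budget would have to change.
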